# Photobiomodulation with simultaneous use of red and infrared light emitting diodes in the treatment of temporomandibular disorder: study protocol for a randomized, controlled and double-blind clinical trial

**DOI:** 10.1097/MD.0000000000014391

**Published:** 2019-02-08

**Keywords:** light emitting diode, photobiomodulation, range of mandibular movements, temporomandibular disorder

## Abstract

**Introduction::**

Temporomandibular disorder (TMD) is considered the main cause of orofacial pain of non-dental origin, and a public health problem. The symptomatology is muscular and/or articular pain, restriction of the mandibular range of motion, and changes in the mandibular movement pattern. Due to its complexity there are already treatments using various forms of therapy. Photobiomodulation using light sources, such as low-level laser or light emitting diodes (LED), with different wavelengths, in a single or combined form, allows one more therapeutic resource to be explored. The objective of this study is to evaluate the effects of photobiomodulation with the simultaneous use of red and infrared LEDs, on pain, range of mandibular movements, and on the electrical activity of masticatory muscles in individuals with TMD.

**Methods::**

A randomized, controlled, double-blind clinical trial is proposed, which will involve 33 individuals (n = 11 per group) of both sexes, ages 18 to 45 years in 3 groups: LED group; placebo group; and control group, submitted to 6 non-consecutive sessions of photobiomodulation totaling 2 weeks of treatment. The Research Diagnostic Criteria for Temporomandibular Disorders—RDC/TMD will be used to assess and determine the participants’ TMD. The pain will be assessed using the Visual Analog Scale – VAS, the mandibular range of motion will be determined with the aid of a digital caliper, and the electrical activity of the masticatory muscles will be verified by electromyography. A mixed plate of 18 red LEDs—660 nm and 18 infrared LEDs—850 nm with power of 3.5 mW per LED, 4.45 mW/cm^2^, radiant exposure of 5.35 J/cm^2^, will be used for photobiomodulation. The irradiated area will be 14.13 cm^2^, and energy of 75.6 J, in the TMJ region and in the bilateral masseter and temporal muscles. Participants from all groups will be reassessed after the first therapeutic intervention, and at the end of treatment.

**Discussion::**

We expect the use of photobiomodulation with LEDs, infra and red, to reduce pain, improve temporomandibular joint function in patients with TMD, and thus improve the general conditions of the patient.

## Introduction

1

Temporomandibular dysfunction—TMD is a set of disorders that encompass the masticatory muscles, temporomandibular joints —TMJ, and the associated structures of the stomatognathic system, or all these structures compromising the system's functionality.^[1]^ It presents a multifactorial etiology^[2]^ and is considered the most common cause of orofacial pain of non-exclusively dental origin.^[3]^

The main symptom is muscular or joint pain, restriction of mandibular range of motion and changes in the pattern of movement of the mandible, but may present with tinnitus, vertigo, muscular incoordination, and biomechanical imbalance of the cervical region.^[4,5]^

Studies have reported that in the Brazilian population, 39.2% of patients had at least 1 sign or symptom of TMD.^[6]^ They occur in all age groups, mainly in adults, with a higher incidence in women in proportions ranging from 3:1.^[7,8]^ Hormones, such as estrogen, may be related to this predisposition.^[9]^ Women with TMD present twice the chance of a painful complaint,^[10]^ and it is already considered an important public health problem, occurring often for long periods and thus interfering with the daily activities of the individual.^[11]^

The complexity of TMDs encouraged the search for treatment of a multidisciplinary team and the use of different forms of therapy,^[12]^ among them, myorelaxant splints,^[13]^ massotherapy resources and mobilizations,^[14,15]^ as well as low level laser photobiomodulation.^[16,17]^ The low-level laser therapy (LLLT) is able to penetrate the tissues by influencing the synthesis, release and metabolism of substances involved in analgesia,^[18]^ stimulating blood flow, promoting anti-inflammatory action,^[19]^ and stands out for its easy application, with the minimum of contraindications and the possibility of shorter treatments.^[20]^ LLLT clinically reduces pain and improvement of mandibular movements.^[21]^

In addition to low-level laser photobiomodulation (LLLT), LED light presents as a further option in the treatment of TMD^[22,23]^ LEDs are semiconductor diodes (p–n junction), which when energized emit light,^[24]^ and present similar results to LLLT, with advantage of the cost of the device,^[25]^ the possibility of using clusters to irradiate larger areas at a single time, ^[26]^ the association of different wavelengths,^[22]^ and absence of side effects.^[27]^ Studies have suggested that LED therapy provides relief of pain, increase in range of motion, and improvement of muscular activity in patients with TMD.

The objective of the proposed study is to analyze the effects of photobiomodulation with simultaneous use in a single light emitting diode device—red LED (660 nm) and infrared LED (850 nm) on pain, amplitude of mandibular movements, and in electrical activity of masticatory muscles in individuals with temporomandibular dysfunction.

At the end of the study, we hope to find with the use of a cluster red and infrared LEDs, a reduction of pain in the masticatory muscles and in the region of the temporomandibular joint, improvement in temporomandibular joint function in TMD patients with the use of LED photobiomodulation and thus, improvement of the general conditions of the patient.

## Materials and methods

2

### Type of study

2.1

A controlled, randomized, double-blind clinical trial will be conducted at the dentistry and physiotherapy clinics of the University Nove de Julho—UNINOVE (Brazil) involving individuals with TMD distributed in 3 groups, including a placebo group and a control group. This protocol study was approved by the Committee of Ethics in Research with Human Beings of the University Nove de Julho (São Paulo, Brazil) under the number 2,962,857. All potential participants will receive clarification on the objectives and procedures, and those who agree to participate voluntarily will sign a declaration of free and informed consent, as stipulated in National Health Council resolutions 466/2012 and 510/2016.

This protocol is in accordance with the 2013 SPIRIT (Standard Protocol Items: Recommendations for Interventional Trials) Statement. The SPIRIT Checklist can be found as an additional file and as Fig. 1. SPIRIT was developed to provide guidance in the form of a checklist of recommended items to include in a clinical trial protocol, to help improve its content and quality.^[28]^

**Figure 1 F1:**
[figure not shown]
Standard Protocol Items: Recommendations for Interventional Trials (SPIRIT) figure as recommended by 2013 SPIRIT statement.

### Test record

2.2

Clinical record: clinicaltrials.gov as NCT 03696706, first published October 5, 2018; https://clinicaltrials.gov/ct2/show/NCT03696706?id=03696706&rank=1

### Sample calculation

2.3

To calculate the sample size, data from the paper by Herpich et al^[22]^ was used. Initially we established an error = 

, where 

 are the mean values of groups 1 and 2. Assuming that both samples have the same size (n_1_ = n_2_), the sample size can be obtained using the following relation: where 

 are the variances of groups 1 and 2, respectively. 
[figure not shown]

Assuming also that the studied groups have normal or approximately normal distribution, and that the sample size will be sufficiently large for a level of significance *α* = 0.05 a value of *Z* = 1.96 is obtained. For the sample size calculation it was also established that the power of the test should be 1 – *β* = 0.80. If the normal distribution hypothesis is rejected, the sample size should be corrected by approximately 5%. We obtain the following sample sizes: LED group: 11 participants, Placebo Group: 11 participants, and Control Group: 11 participants.

### Recruitment and randomization

2.4

Volunteers from both sexes who will participate are students enrolled at University Nove de Julho in São Paulo, Brazil. The recruitment will be simple, since they will already be in the University.

Inclusion criteria: age between 18 and 45 years; clinical diagnosis of TMD, divided by the degrees of this dysfunction based on the Research Diagnostic Criteria for Temporomandibular Disorder—RDC/TMD (according to Table 1); have complete dentition (except third molars); mandibular deviation; and/or deflection.

**Table 1 T1:**
[figure not shown]
Diagnostic subgroups according to RDC/TMD.

Exclusion criteria: present occlusal alterations; use of any type of dental prosthesis; being in orthodontic or physiotherapeutic treatment; necessity of initiating the use of any type of medication during any of the phases of the study.

The randomization will be performed, through the electronic address www.randomization.com, being a 1:1 randomization in blocks, with permutation and change in the size of the blocks. The participants will then be sent for the interventions according to each group, will be evaluated after the first therapeutic intervention, and all will be reevaluated at the end, following the same evaluation sequence used initially (Fig. 2).

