### Interruption of interventions

5.2

The participant will be free to leave the study, at any time, without any kind of loss. If participants become ill or do not adapt to therapy, it will not be possible to continue therapy with LEDs. Interventions will be performed while the participants are in the university, to facilitate their participation and to avoid absences. No adverse effects are expected.

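### The exclusion criteria remove randomised participants who need to start any medication during the study, which can bias the group comparison and shrink groups of 11

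*Protocol article*

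**What the plan says.** Section 2.4 (Recruitment and randomization) of the protocol article gives the exclusion criteria. Most describe a state that can be checked at entry: occlusal alterations, dental prostheses, current orthodontic or physiotherapeutic treatment. The last one does not: "necessity of initiating the use of any type of medication during any of the phases of the study".

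According to sections 2.4, 3.1 and 3.3, the study runs through randomisation, six sessions over two weeks, a reassessment after the first session and a final reassessment. Section 2.4 also says that all participants are reassessed at the end. It does not say whether this includes someone who has meanwhile met an exclusion criterion.

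Pain on a 10 cm visual analogue scale is an outcome (section 3.3), as are mandibular range of motion (3.4) and electromyographic activity (3.5). Section 3.6 plans repeated-measures ANOVA, or Kruskal–Wallis if normality fails. Section 2.3 sets "LED group: 11 participants, Placebo Group: 11 participants, and Control Group: 11 participants". The one correction to that size it mentions, about 5%, is for non-normality and not for removals.

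**The concern.** A criterion that can only be met during follow-up is not an eligibility criterion. It is a rule for removing randomised participants. Any type of medication includes pain relief, and in a pain trial those who come to need it are likely to be in more pain than the rest. If LED reduces pain, fewer LED participants should reach that point than placebo or control participants. Removing those who do takes high pain scores mainly out of the comparison groups and makes those groups look better than they are.

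The likely result is an understated LED effect. If medication starts were commoner in the LED group for some other reason, the distortion could run the other way. Each participant is 1/11, or 9%, of a group, so a few removals matter for both bias and power.

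**Working it through.** **1. Inputs.** From section 2.3: 11 per group; "level of significance *α* = 0.05 a value of *Z* = 1.96 is obtained" (two-sided); "the power of the test should be 1 – *β* = 0.80". The effect and SD behind 11 per group are not legible in the text supplied, so that figure can be neither reproduced nor faulted. Inverting the usual two-mean formula gives the standardised difference it implies:

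d = √2 × (1.96 + 0.8416) / √11 = 1.4142 × 2.8016 / 3.3166 = 1.195 SD.

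With this d, a two-sample t-test at 11 v 11 has 76% power (80% by the normal approximation).

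**2. Assumptions.** The document gives no rate of medication starts. The number removed, the group they come from, and the correlation ρ between medication need and final pain are all assumed below. Pain is taken as normal with SD 1.

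**3. One-sided removal.** The k placebo participants with the greatest medication need are removed, and nobody from LED. The expected three largest of 11 standard normal values are 1.586, 1.062 and 0.729. The placebo mean falls by ρ × (sum of the top k) / (11 − k):

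- k = 1: ρ × 1.586/10 = 0.159ρ
- k = 2: ρ × 2.648/9 = 0.294ρ
- k = 3: ρ × 3.377/8 = 0.422ρ

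Subtracting from 1.195, with t-test power from simulation:

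| Removed from placebo | ρ = 0.5: difference (SD) | Power | ρ = 1: difference (SD) | Power |
|---|---|---|---|---|
| 0 | 1.195 | 76% | 1.195 | 76% |
| 1 | 1.12 | 69% | 1.04 | 66% |
| 2 | 1.05 | 61% | 0.90 | 54% |
| 3 | 0.98 | 54% | 0.77 | 42% |

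Loss of numbers alone does not explain this. With random loss from placebo, the noncentrality is 1.195/√(1/(11 − k) + 1/11), and power is 74%, 71% and 68% for k = 1, 2 and 3.

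**4. Common threshold.** Here the same threshold c on medication need applies in both groups and removes a fraction f of the comparator. With φ and Φ the standard normal density and distribution function, the difference among those who remain is

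d − ρφ(c)/Φ(c) + ρφ(c + ρd)/Φ(c + ρd).

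- f = 10%, ρ = 0.5: c = 1.282, giving 1.195 − 0.097 + 0.035 = 1.13 SD.
- f = 30%, ρ = 1: c = 0.524, giving 1.195 − 0.497 + 0.095 = 0.79 SD.

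Over 10–30% removed and ρ from 0.5 to 1, the 1.195 SD difference therefore appears as 1.13 to 0.79 SD. A true difference of 0.5 SD appears as 0.47 to 0.28 SD. With d = 0 the last two terms cancel and the bias is zero.

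**The case against.** The strongest reply is that this is a condensed article, and analysis sets are commonly left to a fuller document. That would answer a complaint that no analysis set is defined. It does not answer this one, because the article states a rule that excludes people after randomisation. A plan elsewhere that kept everyone would contradict section 2.4, and the text would still need correcting. The statement that all are reassessed at the end does not clearly cover participants who have met an exclusion criterion.

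Other objections do stand, and they limit the size of the point:

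- Treatment lasts two weeks and no rate of medication starts is given. One to three removals from a single group is an assumption.
- Perfect ranking by final pain is a worst case. Drugs unrelated to pain also trigger the rule; they cost numbers but need not bias.
- The model is a two-arm comparison of one final pain value. In the planned repeated-measures analysis of three groups, the removed participants' baselines go too. If their pain was already high at baseline, bias in the group-by-time comparison is smaller. No link is shown between medication need and range of motion or electromyography.

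A reader might infer three stronger points that the document does not support:

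- **That the rule inflates false positives in favour of LED.** With no true effect and the same threshold in each group there is no bias. A raised error rate needs unequal removal, and removal from placebo alone would produce false findings mainly against LED.
- **That section 5.2 removes more participants from analysis.** It says "If participants become ill or do not adapt to therapy, it will not be possible to continue therapy with LEDs". That stops therapy. It does not stop assessment or discard data, and its silence on both may be settled in the full protocol.
- **That the randomised comparison is lost.** It can be biased; whether it is depends on events not yet known.

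**Conclusion.** The point holds as a risk created by a stated rule. Section 2.4 allows randomised participants to be removed for a post-allocation event plausibly tied to the pain outcome. This can bias the comparison, most plausibly towards a smaller LED effect, and it reduces groups that have no stated margin for removals.

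Under the assumptions shown, a true 1.195 SD difference shrinks by 0.08 to 0.21 SD for one to three one-sided removals at a correlation of 0.5, and by 0.16 to 0.42 SD at worst. The common-threshold model gives a loss of about 0.06 to 0.40 SD. These figures are illustrations, not predictions. They depend on assumed removal rates and correlations, on the effect implied by 11 per group, and on a simpler analysis than the one planned.

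**What to change.** Reword the criterion so that it applies only to eligibility known before randomisation. After randomisation, record any medication started, still take the scheduled assessments, and state that the main analysis includes every randomised participant in the assigned group. Report medication starts by group. Use an analysis without these participants as a sensitivity analysis only.

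The cost is a change to one criterion and one sentence on the analysis set. The small downside is that some outcomes will be measured after medication has been taken. The change should be made while follow-up is still possible, because assessments not taken after an exclusion cannot be recovered. It concerns follow-up and the analysis set, not whether medication is permitted.

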**Figure 2 F2:**
[figure not shown]
Flowchart activity.

## Outcomes

3

### Application of the LED therapy protocol

3.1

The sessions will be held in a reserved room, attached to the premises of the dental clinic, free of sound interference. The patient will remain seated, with the Frankfurt plane parallel to the ground. The LED plate shall be coated with clear PVC—disposable plastic for hygiene reasons and to avoid cross—contamination, and a previous facial cleaning with 70% alcohol of the irradiated site shall be performed.

The therapy will be performed with the Sportllux device (Cosmedical, Mauá, SP, Brazil), a plate containing 36 LED points in the regions of the temporomandibular joints, and in the regions of the masseter muscles and anterior portion of the temporal muscles, bilaterally, 3 times a week with interval between sessions, during 2 weeks, totalizing 6 treatment sessions. For the placebo group all measures described for the LED group will be adopted, however, the equipment will remain off. At the time of application only the volunteer to be treated and the researcher responsible will be present, both using specific eye protection. The LED apparatus is composed of a flexible rectangular plate (10 cm/12 cm), which adapts to the format of the area to be treated containing 18 red LEDs—660 nm and 18 infrared LEDs—850 nm, radiant exposure of 5.35 J/cm^2^, total power radiated by LEDs of 63 mW, irradiation of 4.45 mW/cm^2^ per point with an exposure time of 1200 seconds, resulting in an energy of 75 J per point, and total irradiated energy of 453.6 J per volunteer. The application will be in contact with the skin and the area of each beam of 0.7854 cm^2^. All parameters of the LED plates are shown in Table 2.

**Table 2 T2:**
[figure not shown]
Parameters of the LED plate.

### Research diagnostic criteria for temporomandibular disorder—RDC/TMD

3.2

This assessment tool is characterized as a biaxial instrument, composed of detailed physical evaluation of the pattern of buccal opening, vertical extension of mandibular movement, noises of TMJ on palpation for vertical movement extension, mandibular excursive movements, and TMJ noises upon palpation during lateral excursion and protrusion. The questionnaire consists of items involving health in general, oral health, history of facial pain, limitation of openness, noises, habits, bite, tinnitus, diseases in general, joint problems, headache, current behavior, economic and social profile.^[29]^

### Visual analog scale

3.3

This scale will be used for pain assessment and consists of a 10 cm line with 0 (no pain) printed on one end and 10 (debilitating pain) printed on the other end. Participants will be asked to mark a spot on the line that represents the intensity of the current pain. The researcher will then use a ruler to record the distance of zero to obtain a numerical representation of the pain level. These procedures will be performed before and after the first session and at the end of treatment.

### Mandibular range of motion

3.4

The volunteer will be instructed to open his mouth as much as possible. The maximum vertical mandibular movement will be measured (in mm) as the distance between the maxillary and mandibular central incisors determined with the aid of a digital caliper. The volunteer will then be instructed to put pressure on the lower teeth with the mouth open and move the jaw to the right and left to determine the excursion (distance between the upper and lower midpoints). These procedures will be performed before and after treatment. This procedure composes the clinical evaluation of RDC/TMD.

### Recording of electromyographic signals

3.5

We will use a signal conditioning module with frequency bandpass filter between 20 and 1000 Hz, common mode rejection index >120 db. All data will be collected and processed using a 16-bit analog/digital converter with a sampling frequency of 2 kHz. Before placing the electrodes, the volunteer's skin will be cleaned with 70% alcohol to reduce the impedance,^[30]^ and the volunteer is asked to perform the trichotomy in the region if necessary. Active and disposable surface electrodes positioned in the area with the largest muscular volume of the masseter will be used, directed from the angle of the mandible to the lateral corners of the eyes, parallel to their fibers. In the same way, the anterior fibers of the temporal muscle will be palpated, and the electrodes will be positioned parallel to their fibers, bilaterally, performing muscular function.^[30]^ Participants will remain seated in a chair, with their backs fully supported by the backrest, Frankfurt plane parallel to the ground, eyes open, feet parallel and resting on the ground, and arms resting on the lower limbs.

The EMG signal will be captured in the following situations: postural position of mandibular rest; in non-habitual masticatory activity (isotonic) and; in isometry, that is, maximum voluntary contraction.^[31]^ In the isometry situation we will perform the evaluation with the interposition of parafilm and in the maximum usual intercuspation, and each situation will be repeated 3 times, with an interval of 2 minutes between each record for isotonia and isometry. In the situation of unusual chewing (isotonic) and in the isometry with interposition of parafilm, the volunteer will place it between the lower and upper premolars, first and second molars bilaterally. The Parafilme—M will be folded, leaving the size of approximately 35 mm, 15 mm wide and 3 mm thick, which obtained the lowest values of variability in electromyography records for masticatory activity, positioned bilaterally, or unilaterally between the inferior and superior premolars, first and second molars.^[32]^

### Statistical analysis

3.6

The results obtained will be submitted to the Shapiro-Wilk statistical analysis to evaluate the normality. If the data obeys a Gaussian curve, the Analysis of Variance (ANOVA) of repetitive measures will be used with significance level *p* < 0.05. If the data are not parametric, the Kruskal–Wallis test will be used.

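### A Shapiro-Wilk test on the raw results, rather than a look at the model residuals, decides whether the repeated-measures ANOVA is run, so a valid planned analysis can be discarded

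*Protocol article*

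**What the plan says.** Section 3.6 (Statistical analysis) of the protocol article sets a two-way rule. First, "The results obtained will be submitted to the Shapiro-Wilk statistical analysis to evaluate the normality". Then: "If the data obeys a Gaussian curve, the Analysis of Variance (ANOVA) of repetitive measures will be used". Otherwise: "If the data are not parametric, the Kruskal–Wallis test will be used". The significance level of 0.05 is attached to the ANOVA; none is given for the Shapiro-Wilk test. Residuals are not mentioned. The section does not say whether values are tested pooled, per visit or per group-by-visit cell, or what follows if some sets pass and others fail.

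Section 2.3 (Sample calculation) gives the sizes: "LED group: 11 participants, Placebo Group: 11 participants, and Control Group: 11 participants". Section 3.3 has pain measured three times (before and after the first session, and at the end of treatment), which makes nine group-by-visit cells of 11 values. Section 3.4 describes range of motion before and after treatment, which makes six cells.

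**The concern.** The normality assumption of a repeated-measures ANOVA concerns the errors around the group-by-visit means. It does not require the results themselves to follow one Gaussian curve. If raw values are pooled over groups and visits, a real LED effect makes them a mixture of shifted normal curves. The test can then reject because the means differ, although the ANOVA's assumption holds exactly.

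The choice of analysis would then depend partly on the treatment effect or on chance. The choice matters because Kruskal-Wallis compares independent groups. It has no visit term and no group-by-visit term, so a failed test replaces an analysis of change over time with one that cannot address it directly.

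**Working it through.** **1. Inputs.** From the article: three groups of 11, three pain assessments, two-sided 0.05 in the sample size ("a value of *Z* = 1.96 is obtained") and power 0.80. Assumed: Shapiro-Wilk level 0.05, within-person correlation 0.5 or 0.7, errors exactly normal with SD 1.

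**2. Effect size implied by the design.** The stated 11 per group cannot be reproduced, because the formula and the means and variances are images missing from the text. That is not a fault of the plan. Back-solving the usual two-mean formula:

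d = (z₀.₉₇₅ + z₀.₈₀) × √(2/n) = (1.960 + 0.842) × √(2/11) = 2.802 × 0.4264 = 1.195 SD.

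So about 1.2 SD is the reference effect. If the power term had been left out, the implied effect would be 1.960 × 0.4264 = 0.84 SD.

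**3. Simulation.** Each setting used 2,000 to 4,000 trials of 3 × 11 × 3 values, so the Monte Carlo standard error is at most √(0.5 × 0.5 / 2,000) = 1.1 points. Two time courses were used for the LED-placebo difference:
- gradual: half after the first session, full at the end, no placebo change;
- immediate: full from the second assessment, with a placebo change of 0.3 SD.

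Every data set satisfies the ANOVA's normality assumption. The table gives the percentage of trials in which Shapiro-Wilk rejects; ranges span both correlations and repeated runs.

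| What is tested | No effect | 1.2 SD | 2 SD | 3 SD |
|---|---|---|---|---|
| (a) 99 raw values, gradual | 6–12 | 8–11 | 20–26 | 71–73 |
| (a) 99 raw values, immediate | 7–11 | 10–15 | 42–47 | 94–95 |
| (b) 33 raw values at one visit | 5 | 4–5 | 8–9 | 30–37 |
| (c) any of nine cells of 11 | 37–39 | 37–39 | 37–39 | 37–39 |
| Residuals, 99 pooled | 6–13 | 6–13 | 6–13 | 6–13 |
| Residuals, 33 at one visit | 4–6 | 4–6 | 4–6 | 4–6 |

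**4. Reading (a), pooled.** Rejection climbs with the effect for raw values and not for residuals. At 1.2 SD the excess over pooled residuals is about 1 point or less if the effect is gradual and at most about 5 points if it is immediate. It becomes material from about 2 SD, which is 2/1.195 = 1.7 times the implied design effect; 3 SD is 2.5 times. Pooled residuals exceed 5% because repeated values from one person are not independent.

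**5. Reading (b), one visit across groups.** There is no excess at 1.2 SD and a clear one only near 3 SD.

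**6. Reading (c), cell by cell.** Treating the cells as independent, the chance of at least one false failure is 1 − 0.95⁹ = 0.37 for pain and 1 − 0.95⁶ = 0.26 for range of motion as described in 3.4. The simulated 37–39% agrees for nine cells. Within a cell, a raw value and its residual differ only by the cell mean, a constant, and Shapiro-Wilk is unaffected by a constant. Nine tests on cell residuals would give the same rate.

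**The case against.** The strongest reply is that three sentences in a journal article are being read too literally. Saying that results are submitted to a normality test is common shorthand, and the unit and level of testing are ordinarily left to a fuller document that is not shown. That has force: the missing unit and level are not in themselves a fault. But the section does state the tested object, the test and the consequence, and as stated the object is the wrong one.

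Two stronger readings are tempting, and the documents support neither.

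- A reader might infer that a working treatment will make the data fail and so remove the ANOVA. This is a probability, not a certainty. It needs values pooled across groups and, to be large, an effect well above the one the sample size implies. At 1.2 SD the raw-value test behaves much like the residual test, and at 0.84 SD there is no excess. The highest rates also need the full effect after one session. Section 4 reports less pain after a single application in the study used for the sample size, so that time course is possible, but nothing in the article fixes it.
- A reader might infer that the 37% shows the harm of testing raw values. It does not. It arises from nine tests at n = 11, and only under a rule, not stated in 3.6, that a single failing cell switches the analysis.

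**Conclusion.** The point holds in limited form. Section 3.6 lets a significance test on raw results choose the analysis, although the ANOVA's assumption concerns residuals. The gate can discard a valid planned analysis by chance under any of the readings or, if values are pooled across groups, because the effect is very large. At the effect the design implies, the cost of testing raw values instead of residuals is small under pooling and nil when a single visit is tested. The large figure at that effect, 37%, belongs to multiplicity under an unstated rule.

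These sizes rest on normal errors, the assumed 0.05 level, correlations of 0.5 to 0.7 and the two assumed time courses. The 1.2 SD reference is back-solved and not quoted from the article. I would rate this as a change to consider: the improvement is clear and cheap, but the expected harm at plausible effects does not call for more.

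**What to change.** Reword 3.6 along these lines: *Each outcome will be analysed with the planned repeated-measures ANOVA. Normality will be judged on the residuals of that model, chiefly by Q-Q plot. A Shapiro-Wilk test on the residuals, if reported, is descriptive and does not select the analysis.* No significance test on raw pooled results, or cell by cell, should act as the switch. The Shapiro-Wilk test should stay descriptive even on pooled residuals, because it still rejects valid data in about 6–13% of trials. The section should also say in advance what a clear departure on the Q-Q plot leads to.

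The cost is two or three sentences of analysis wording. It needs no extra participants, measurements or visits, and the sample size is unaffected.
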